#### Serologic immune markers

Because it is anticipated that the immune response towards GBM treated with CIRT will be distinct from the response towards tumors treated with standard, low-LET radiotherapy, peripheral blood levels of key immunologic markers will be assayed and compared with baseline levels. Several studies have reported that aberrant levels of cytokines and subtypes of circulating T cells can be detected in the blood samples of glioma patients and can serve as markers of tumor biology/immune state, virulence, and progression [46–49]. The markers to be assayed play critical roles in either the pro-inflammatory/anti-tumor or anti-inflammatory/pro-tumor immunity and are summarized in Table 2. The dual purpose of this data collection will be to both characterize the immune responses towards GBM treated with CIRT and to inform future immunotherapy trials which use this radiotherapeutic modality.

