## Methods and design

### Study design

The purpose of this trial is to first determine, in a Phase I dose escalation study, the maximal safe induction CIRT boost to the residual tumor in malignant glioma patients [GBM or anaplastic astrocytoma (AA)] that can be given to patients in addition to adjuvant radiotherapy at the standard dose (i.e., 60 GyE in 30 fractions). The rationale for this approach is to provide a different form of radiotherapy; one with a higher LET, having a different mode of tumor-killing, and possessing a greater overall tumor-killing ability due to its weaker dependence on oxygenation for efficacy, to the site of disease immediately after surgery when the number of tumor cells and extent of hypoxia are at their greatest. We anticipate that these factors will result in a shift from the usual pro-tumor immunosuppression, fostered by tumor microenvironment, into one that promotes a greater inflammatory and anti-tumor immunity environment.

In the second stage of this trial, the Phase III, the following hypothesis will be tested: When induction CIRT boost with the maximal safe dose (determined in Phase I) is given prior to standard PRT, whether this strategy will result in a prolonged OS of GBM patients without provoking additional toxicity as compared with standard PRT.

A secondary aim of this study is to determine if there are immunologic response profile differences between those receiving CIRT boost and those who do not, such that additional immunotherapeutic agents can be administered in future trials to synergize and augment the effects of the CIRT boost.

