##### Serologic immune markers

To ascertain the specific immune response profile to the induction CIRT boost, all patients enrolled into the Phase III study will have their blood samples investigated before irradiation to establish the baseline profile of serologic immune markers (detailed in Table 2 and between the fifth and sixth fractions of PRT to determine the changing profile. Those who receive the induction CIRT boost will have an additional serologic marker detection between the last fraction of the boost and the first proton fraction. The overall Phase III schema is illustrated in Fig. 1.

**Table 2 Tab2:** Serologic immune markers of GBM

Marker	Function/correlative findings	Assay
Pro-inflammatory/anti-tumor		
IL-1β	Stimulates cytotoxicity; serum levels decrease during low-LET radiotherapy [55]	Serum ELISA
IL-6	Pro-inflammatory cytokine, defective expression from lymphocytes in patients with glioma [56]	Serum ELISA
TNF-α	Promotes cell-directed cytotoxicity; reduced levels are associated with GBM [57]	Serum ELISA
CD3+ lymphocytes	Direct immune-mediated cytotoxicity; increased levels are associated with prolonged survival [58]	Flow cytometry
CD8+ lymphocytes	Direct immune-mediated cytotoxicity, increased levels are associated with prolonged survival [58]	Flow cytometry
Anti-inflammatory/pro-tumor		
IL-4	Induces immunosuppression and tumor tolerance; high levels are associated with GBM [57]	Serum ELISA
IL-10	Induces immunosuppression and tumor tolerance; high levels are associated with GBM [57]	Serum ELISA
TGF-β	Promotes proliferation and immune escape of GBM [59]	Serum ELISA
Regulatory T cells	Secrete IL-10 and TGF-β, suppress CD8-dependent tumor-specific cytotoxicity, and elevated in peripheral blood of GBM patients [60]	Flow cytometry

*GBM* glioblastoma, *IL* interleukin, *TNF*-*α* tumor necrosis factor-α, *TGF*-*β* transforming growth factor-β, *LET* linear energy transfer, *ELISA* enzyme-linked immunosorbent assay

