### TMZ dosing and schedule

Conventional oral chemotherapy with TMZ (75 mg/m^2^) will commence on the first day of PRT in both arms. TMZ will not be administered during the CIRT boost in the experimental arm so as not to suppress the desired shift towards an anti-tumor immune response and the effect against glioma cells that have infiltrated the brain parenchyma at a distance from the primary tumor site.

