#### Toxicity rates

The CTCAE v. 4.03, or the most recent update, will be used to assess all toxicity and adverse events observed during and after the completion of treatments [38]. Patients will be evaluated weekly by complete history taking, physical examination, and blood chemistry tests to determine the safety and toxicity of all treatments in this clinical trial. These evaluations will be conducted at each on-treatment appointment and at each clinical follow-up visit.

Efforts will be made to use bevacizumab as a first-line treatment for radiation-induced tumor/cerebral edema, based on its efficacy and minimal immunosuppressive effects [39–42]. For refractory cases or those in which bevacizumab is not available, dexamethasone will be used per routine protocols and noted in conjunction with serologic immune marker studies.

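### The immune aim is a difference between arms, but the only comparison stated for marker levels is with baseline, which at the shared sample cannot isolate the boost

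*Protocol article*

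**What the plan says.** The Study design section gives a secondary aim that contrasts the arms: to "determine if there are immunologic response profile differences between those receiving CIRT boost and those who do not". The results are meant to guide immunotherapy in later trials.

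The sampling schedule is in the Serologic immune markers paragraph of the Phase III trial design:

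- **Baseline, both arms:** "all patients enrolled into the Phase III study will have their blood samples investigated before irradiation".
- **On treatment, both arms:** "between the fifth and sixth fractions of PRT to determine the changing profile".
- **Boost arm only:** patients given the boost "will have an additional serologic marker detection between the last fraction of the boost and the first proton fraction".

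The TMZ dosing and schedule section starts temozolomide (TMZ) on the first day of proton therapy (PRT) in both arms and adds that "TMZ will not be administered during the CIRT boost in the experimental arm".

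The comparison itself is in the Serologic immune markers paragraph under Treatment response assessments: "peripheral blood levels of key immunologic markers will be assayed and compared with baseline levels". The Biomarker analyses section relates marker levels to OS, PFS and response. The Outcome analyses section describes between-arm comparisons for survival and adverse events, but none for the markers.

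On steroids, the Toxicity rates section makes bevacizumab the first choice for edema. Where it fails or is unavailable, "dexamethasone will be used per routine protocols and noted in conjunction with serologic immune marker studies".

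**The concern.** The aim and the stated comparison answer different questions. The aim asks whether patients given the boost differ from those who are not. The stated comparison asks whether a patient's levels have moved since baseline. They may have moved for reasons common to both arms. The protocol itself calls TMZ immunosuppressive (Induction CIRT boost rationale, Discussion), and its Table 2 records that IL-1β falls during low-LET radiotherapy. A change at the shared sample is therefore to be expected without any boost.

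If the comparison is carried out as worded, a marker that moves in the boost arm could be reported as a response to carbon ions when protons and TMZ produced it. A real boost effect could equally be hidden by a shared effect in the other direction. Since the readout is to inform later immunotherapy trials, either error would carry forward.

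**Working it through.** The plan gives no figure for this point, so the check sets out what each sample contains and then what each contrast estimates.

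**1. Exposure at each sample** (Phase III trial design; TMZ dosing and schedule; Table 3)

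| Sample | Boost arm | Control arm |
|---|---|---|
| Before irradiation | none | none |
| After boost, before protons | boost only; no protons, no TMZ | not drawn |
| Between PRT fractions 5 and 6 | boost + 5 × 2 = 10 GyE protons + TMZ since PRT day 1 | 10 GyE protons + TMZ since PRT day 1 |

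**2. What each contrast estimates at fraction 5–6.** Let B be the boost effect and S the shared effect of protons and TMZ, taken as additive.

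- Change from baseline, boost arm: B + S
- Change from baseline, control arm: S
- Difference between arms: (B + S) − S = B

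For illustration, assume B = +0.5 SD and S = −0.8 SD. The boost arm then changes by 0.5 − 0.8 = −0.3 SD, the wrong sign for the boost. The control arm changes by −0.8 SD. The difference is −0.3 − (−0.8) = +0.5 SD, which recovers B. A simulation with 122 and 121 patients gave −0.30 and +0.50.

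**3. The post-boost sample.** Its change from baseline is B plus whatever else happens in that interval, such as further time since surgery or a change in steroids. With no control sample at that time, those parts cannot be subtracted.

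**4. Size of effect the between-arm contrast can detect.** With 122 and 121 patients, 80% power and two-sided 5%:

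- one marker: (1.960 + 0.842) × √(1/122 + 1/121) = 2.802 × 0.1283 = 0.36 SD
- at 5%/9, for the nine markers of Table 2: 0.46 SD
- with 116 and 115 patients, after the 12 planned dropouts: 0.37 and 0.48 SD

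The SD here is that of the quantity analysed.

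**5. Baseline adjustment against change scores.** With equal variance at both times and baseline correlation r, in units of the marker variance, the change score has variance 2(1 − r) and ANCOVA has 1 − r². The ratio is (1 + r)/2. The protocol gives no r, so a range is shown.

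| Assumed r | Change score | ANCOVA | Ratio |
|---|---|---|---|
| 0.3 | 1.40 | 0.91 | 0.65 |
| 0.5 | 1.00 | 0.75 | 0.75 |
| 0.7 | 0.60 | 0.51 | 0.85 |

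**The case against.** The strongest reply is that the baseline wording only defines the measure, and that the between-arm aim supplies the contrast. On that reading the plan is change from baseline compared between arms, which is valid under randomisation, and the choice of model belongs in an analysis plan that is not shown. Part of this stands. The wording does not exclude comparing changes between arms, and ANCOVA over change scores is a gain in precision, not the correction of a bias. It does not dispose of the point. The article does state how the markers will be compared, and as stated that does not answer its own aim.

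A reader might go further in four ways that the documents do not support.

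- **That the trial cannot show the between-arm difference.** It can: both randomised arms have the baseline and fraction 5–6 samples.
- **That every boost-arm sample mixes the boost with protons and TMZ.** The post-boost sample precedes the first proton fraction, and TMZ is withheld during the boost. The rationale section gives less confounding by PRT as a reason for giving the boost first, and that is a real strength.
- **That each arm will be tested separately against baseline and the two significance results compared.** The plan never specifies this, so error rates derived from it do not apply.
- **That dexamethasone will be used more in the boost arm.** This is possible but nowhere documented. It is second-line, and its use is recorded with the marker studies.

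**Conclusion.** The point holds for the stated comparison, not for the data. As worded, the marker comparison does not address the between-arm aim. At the fraction 5–6 sample, a within-arm change includes the effect of 10 GyE of protons and of TMZ, and so cannot be attributed to the boost. The post-boost sample avoids that mixture but has no concurrent control for time since surgery or steroid changes.

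The contrast between randomised arms at fraction 5–6 removes the shared part. It can detect about 0.36 SD for a single marker and about 0.46 SD at 5%/9, if all planned patients provide samples. The 25% reduction in variance from baseline adjustment rests on the assumed r = 0.5; over r = 0.3 to 0.7 it runs from 35% to 15%. The −0.3 and +0.5 SD figures illustrate the mechanism with assumed effects and do not predict the result.

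One limit remains. PRT starts one week after the first boost fraction, so at the shared sample the boost arm is about one week further from its first irradiation. The contrast therefore estimates the effect of the boost strategy including that extra week.

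**What to change.** In the Serologic immune markers paragraph under Treatment response assessments:

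1. State that the immune comparison is between the randomised arms at the fraction 5–6 sample, by ANCOVA adjusted for the baseline level of the marker, with cytokines on the log scale.
2. Describe the post-boost sample as a within-arm description of change, not by itself as evidence of a CIRT-specific effect.
3. If an analysis leaves out samples drawn on dexamethasone, label it a sensitivity analysis. Steroid use after randomisation may be affected by the arm, so excluding on it can introduce selection.

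This costs wording only: no new samples, visits or patients, and dexamethasone use is already to be noted. The downside is that the post-boost sample will support a weaker claim, and that the extra week in the boost arm should be acknowledged when the contrast is reported.

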### *MGMT* promoter methylation status

When possible, each enrolled patient will have their tumor tissue specimens investigated to assay the presence or absence of *MGMT* promoter methylation using methylation-specific polymerase chain reaction (PCR) as previously described [50]. *MGMT* promoter methylation occurs in approximately 50% of all GBM patients. It is associated with the biologically aggressive secondary and pro-neural subtypes and, not surprisingly, represents a favorable prognostic and predictive factor for an improved response to both irradiation and TMZ [51]. The presence of this molecular biomarker will be subjected to correlative, subset outcome and response analyses.

### Treatment after tumor progression

After completion of chemoradiotherapy, further treatment, including surgical resection, a second course of irradiation, systemic chemotherapy, or targeted therapy may be clinically necessary in case of disease recurrence or progression. These treatment decisions will be made at the discretion of the treating physician and/or team.

### Follow-up

After completion of treatment, all patients will be required to be followed-up regularly, indefinitely or until death, according to our institutional follow-up protocol. The first and second follow-up visits will be scheduled at 1 and 3 months after the completion of radiotherapy. Unless otherwise clinically necessary, follow-up sessions will then be scheduled every 3 months in the first 3 years, every 6 months in the following 2 years, and annually thereafter. Each follow-up will include a complete history taking and physical examination, MRI of the brain, and blood chemistry tests (including complete blood counts, serum electrolyte levels, and liver/renal function test).

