#### Phase III

##### Experimental arm

A total of 122 patients will be enrolled into this arm and undergo an induction CIRT boost to the residual gross tumor volume. The dose of the induction boost will be determined in Phase I of the trial. One week after the first fraction of the induction boost, a standard PRT (60 GyE in 30 fractions) with concurrent daily oral administration of TMZ at 75 mg/m^2^ will commence.

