CIRT and PRT planning: Radiotherapy will be planned using the Syngo treatment planning system (Siemens, Erlangen, Germany) and delivered using the IONTRIS intensity-modulated raster scan system (Siemens, Erlangen, Germany) as previously described [37]. Briefly, CIRT and PRT will be performed once a day, 5 days a week. The patient’s position will be verified using a craniofacial X-ray before radiotherapy, and set-up deviations of more than 2 mm will be corrected. CIRT is planned with RBE calculated using the local effect model (LEM). The RBE values of CIRT at 3, 4, 5, and 6 GyE will be 3.3, 2.9, 2.6, and 2.4, respectively.

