#### Progression-free survival

PFS will be defined as the time between the first day of treatment and the date of disease recurrence confirmed by imaging (either on routine follow-up or symptom-directed imaging studies). Patients who do not succumb or who are not lost to follow-up and present with no evidence of disease progression will be censored at the date of the last follow-up.

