### Treatment response assessments

#### Imaging

To assess the initial responses to the CIRT boost, MET/FET PET or MRS will be performed at 2 weeks after the initiation of CIRT in the experimental arm. To assess the overall treatment response, MET/FET PET or MRS will be performed at 4 weeks after the completion of PRT in both arms. The target lesion will be evaluated using the response assessment in neuro-oncology (RANO) criteria [43] with interpretation modifications [44, 45] and is summarized below:Complete response (CR): Complete disappearance of all tumors on consecutive computed tomography (CT) or MRI scans sustained for at least 1 month, without the use of steroids.Partial response (PR): An observed ≥ 50% decrease in the area of contrast enhancement on consecutive CT or MRI sustained for at least 1 month. Doses of steroids must be stable or decreased, and the patient must be neurologically stable.Progressive disease (PD): An observed ≥ 25% increase in the area of contrast enhancement or any new tumor on CT or MRI.Stable disease (SD): All other situations.

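### Scheduled follow-up MRIs fall about one week later after the PFS origin in the experimental arm, which tilts exploratory PFS modestly towards the carbon ion boost

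*Protocol article*

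**What the plan says.** All of this is in the Protocol article.

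- **PFS origin and event** (Progression-free survival): "PFS will be defined as the time between the first day of treatment and the date of disease recurrence confirmed by imaging". Detection may be "either on routine follow-up or symptom-directed imaging studies".
- **Scan calendar** (Follow-up): "The first and second follow-up visits will be scheduled at 1 and 3 months after the completion of radiotherapy", after which "follow-up sessions will then be scheduled every 3 months in the first 3 years". The content of a visit is fixed too: "Each follow-up will include a complete history taking and physical examination, MRI of the brain".
- **Treatment start** (Experimental arm): "One week after the first fraction of the induction boost, a standard PRT (60 GyE in 30 fractions" begins. The control arm has no boost, so its first treatment day is its first proton fraction.
- **Treatment pace** (Radiotherapy planning): "CIRT and PRT will be performed once a day, 5 days a week".
- **Response imaging** (Imaging): "MET/FET PET or MRS will be performed at 4 weeks after the completion of PRT in both arms". The experimental arm also has a PET or MRS 2 weeks after the boost starts, with no control counterpart.
- **Status of PFS** (Study objectives; Outcome analyses): a secondary endpoint of Phase III, analysed by the same method as OS but labelled exploratory.

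**The concern.** The PFS clock and the scan calendar start from different dates, and the gap between those dates differs by arm. Proton therapy has the same length in both arms, so radiotherapy ends about one week later after the PFS origin in the experimental arm, and the scheduled scans follow that end date.

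A week is short against scans three months apart, but the log-rank test works on the order of events. Progressions found at routine scans cluster at the visits. At each round the control cluster is dated first, while the matching experimental patients still count as progression-free. The same biology in both arms can then give an HR below 1. The error runs in one direction, towards the boost, and it grows as visits are kept more punctually. At stake is the reported PFS hazard ratio and its p-value.

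**Working it through.** **The plan's own figures.** The article gives no assumption or calculation for PFS. Its OS figure of 192 events reproduces (Schoenfeld formula, HR 16/24, 80% power, two-sided 5%: 191) and is not at issue.

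**Step 1: the calendars.** Thirty fractions at five per week take 6 weeks. Radiotherapy ends at about day 42 in the control arm and day 7 + 42 = 49 in the experimental arm. With months of 30.44 days, scheduled MRIs fall at these weeks from the PFS origin:

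| Visit after radiotherapy | 1 mo | 3 mo | 6 mo | 9 mo | 12 mo |
|---|---|---|---|---|---|
| Control | 10.3 | 19.0 | 32.1 | 45.1 | 58.2 |
| Experimental | 11.3 | 20.0 | 33.1 | 46.1 | 59.2 |

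The lag is a constant 1 week.

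**Step 2: why one week moves the test.** Assume no true effect, exponential PFS with a 7-month median (λ = ln 2 / (7 × 30.44) = 0.00325 per day), 122 v 121 patients, and detection only at exactly kept visits. Take the 6-month visit:

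- At risk: experimental 122 × exp(−0.00325 × 140.3) = 77.3; control 121 × exp(−0.00325 × 133.3) = 78.4.
- Progressing in the 91.3-day interval: 1 − exp(−0.00325 × 91.3) = 25.7%, so 19.9 experimental and 20.2 control.
- The control cluster comes first: experimental O − E = 0 − 20.2 × 77.3/155.7 = −10.0.
- The experimental cluster comes a week later, with control at risk now 58.2: 19.9 − 19.9 × 77.3/135.5 = +8.5.
- Net for the round: −1.5, although the two arms have the same hazard.

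The net terms over the visits within 36 months are −0.55, −0.84, −1.47, −1.09, −0.81, −0.60, −0.45, −0.33, −0.25, −0.18, −0.14 and −0.10, in total −6.8. The summed log-rank variance is 51.6, so the apparent HR is exp(−6.8/51.6) = 0.88. This agrees with the simulated 0.87 below.

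**Step 3: simulation under no true effect** (122 v 121, 1000 runs per cell, 36 months of follow-up). Median PFS, visit scatter and the share found by symptom-directed imaging are assumptions, since the article gives none. Cells show the apparent HR and, in brackets, the one-sided false-positive rate in favour of the boost (nominal 2.5%).

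| Setting | Median 5 mo | 7 mo | 10 mo |
|---|---|---|---|
| No lag, exact visits | 1.00 (3.0%) | 1.00 (2.9%) | 1.00 (2.0%) |
| 7-day lag, exact visits, scheduled scans only | 0.82 (26.7%) | 0.87 (16.1%) | 0.92 (9.5%) |
| Visits ±7 days, scheduled scans only | 0.89 (13.9%) | 0.93 (9.0%) | 0.95 (5.1%) |
| Visits ±14 days, scheduled scans only | 0.95 (6.3%) | 0.96 (5.7%) | 0.98 (3.4%) |
| ±7 days, 30% symptom-detected | 0.94 (7.4%) | 0.96 (4.6%) | 0.97 (5.2%) |
| ±7 days, 30% symptom-detected, 2-week scan can date progression | 0.96 (6.1%) | 0.97 (5.5%) | 0.98 (5.1%) |

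Letting the end of radiotherapy also vary by 0 to 14 days gives 0.98 (3.7%) in the last row at 7 months. With ±14 days, 50% symptom-detected and that same spread, the HR is 1.00 (3.0%). With 1000 runs, a rate near 5% has a standard error of √(0.05 × 0.95/1000) = 0.7 percentage points.

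Removing the lag restores an HR of 1.00, so the calendar is the cause.

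**The case against.** The best case against raising this has three parts.

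- **PFS carries no confirmatory weight.** The Outcome analyses section labels it exploratory and gives it no alpha. OS runs from pathological confirmation to death and depends on no scan, so the sample size and the interim rule are untouched. This stands, and it limits the severity. A reader might infer that the lag threatens the trial's main conclusion or inflates a controlled error rate; the article supports neither.
- **Not every scan is lagged.** Symptom-directed imaging counts for PFS and follows no calendar, and the experimental-only 2-week scan pulls slightly the other way. This also stands. A reader might infer that every experimental-arm scan is late and that the HR near 0.87, or a false-positive rate of 16% or more, is what to expect. That requires almost exact visits and no symptom-directed detection, which the article does not suggest.
- **Visit windows and interval-censored analyses belong in a fuller document that is not shown.** True, and their absence is not criticised. The two dates, however, are stated rules. Followed as written they produce the lag, and nothing in the article offsets it.

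Moving only the PFS origin to randomisation might look sufficient. It is not, because the scans would still follow the end of radiotherapy.

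**Conclusion.** The point holds as a minor one. The stated rules put every scheduled follow-up MRI, and the imaging 4 weeks after proton therapy, about 7 days later after the PFS origin in the experimental arm. The resulting bias favours the boost.

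Its likely size is an apparent HR of about 0.95 to 0.99 with no true effect, and one-sided false positives of about 2 to 6%. The range of about 0.82 to 0.92 applies only with exact visits and all progressions found at scheduled scans. These sizes rest on an assumed exponential PFS with a median of 5 to 10 months, assumed visit scatter and an assumed symptom-detected share. The one-week lag itself comes from the text, given treatment delivered on schedule. Recorded progression dates move by about a week at most. It is worth correcting because PFS is a named secondary endpoint, the bias has a known direction, and the remedy is cheap.

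**What to change.** **Preferred.** In Follow-up, time the surveillance MRIs used for PFS at the same weeks in both arms from one common date, such as randomisation. Use that date as the PFS origin too. Keep the present number of scans and intervals, with the first scan at a week that lies after the end of radiotherapy in both arms. In Imaging, state that the experimental-only 2-week scan does not date progression for PFS. Either place the imaging 4 weeks after proton therapy on the common calendar or state that it serves response assessment only.

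The cost is a few sentences in three sections (Follow-up, Progression-free survival and Imaging) and no extra scan. The gap from the end of radiotherapy to each scan will then differ by one week between arms.

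**Alternative.** Keep the visits as they are and analyse PFS by visit round, grouped or interval-censored. Interval censoring on actual scan dates is the cleaner choice. Pure grouping treats the first interval as equal in the two arms, although it is 49 + 30.4 = 79.4 days against 42 + 30.4 = 72.4 days, which leans slightly against the boost. The cost is a little more analysis work.
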